#### Skeletal Muscle Mass

Total body SMM will be measured using multifrequency segmental bioimpedance analysis (Tanita MC-780; Tanita Corporation) [41]. The measurement procedure requires the child to stand in bare feet on the analyzer and to hold a pair of handgrips, 1 in each hand for approximately 15 seconds. Subsequently, the Skeletal Muscle Index (SMI) will be calculated by dividing the individual SMM (kilogram) by height (m^2^; ie, SMI=SMM/height). The Tanita device has shown excellent test-retest reliability [42]. High significant correlations (correlation coefficients ≥0.85) were shown for body composition values in children and adolescents, between bioimpedance analysis and dual-energy X-ray absorptiometry (which is the golden standard for the measurement of muscle mass) [43].

#### Muscle Strength

Handgrip strength (kilogram) will be measured in sitting position with the elbow flexed at 90° using a hydraulic Jamar handheld dynamometer (Sammons Preston). During the measurement the child will be verbally encouraged to achieve a maximum performance. For both the dominant and nondominant hand the mean score of 3 repeats will be calculated. Raw results will be compared with population-based age- and sex-specific reference values [44]. Handgrip dynamometry showed good validity (intraclass correlation coefficients [ICCs] 0.73-0.91) with high reproducibility in children from the age of 4 years and has excellent test-retest reliability (ICC 0.91-0.93) [45,46], and the measurement was feasible in children with leukemia [47].

#### Fatigue

Fatigue-related complaints will be assessed using the validated Dutch version of the Pediatric Quality of Life Inventory (PedsQL)-Multidimensional Fatigue Scale (MFS) [48,49]. This questionnaire consists of 3 scales: General Fatigue, Sleep/Rest Fatigue, and Cognitive Fatigue, resulting in subscores and in a total fatigue score. We will use parent proxy reports for children aged 2-4, 5-7, 8-12, and 13-18 years, as well as self-report versions for children aged 8-12 and 13-18 years. The results of PedsQL-MFS will be compared with Dutch normative values from the general population [48]. The internal consistency of the Dutch version of the PedsQL-MFS has been reported as satisfactory (Cronbach coefficient α >.70), test-retest reliability was good (ICC 0.68-0.84), and the interobserver reliability varied from moderate to excellent (ICC 0.56-0.93) [48]. The original version of PedsQL-MFS has been validated in patients with pediatric cancer, 50% of whom had ALL [49], and the Dutch version has been used previously in studies in children with ALL [28,50].

#### Walking Speed

The TUG will be used to asses walking speed. A chair, without arm rests, allowing the child to sit with his feet flat on the floor and his hip and knees flexed at 90° will be used. The chair will be positioned at a 3-m distance from a wall. The child will be asked to get up from the sitting position and walk “as fast as he can, without running” to the wall and touch a self-chosen picture on the wall, turn around without using the wall for support, walk back to the chair, and sit down. During the test verbal instructions will be repeated and encouragements are made. Time is recorded from the “go” cue to when the child is sitting down in the chair. The mean time of 3 trials will be considered as the test result [51]. The results of the test will be compared with age-specific reference values [52]. The TUG has shown excellent test-retest reliability (ICC 0.80-0.98) and interobserver reliability (ICCs 0.86 to 0.99) in the pediatric population [53], and the measurement was feasible in children with leukemia [47].

^a^Standardized method to quantify the quality of rising by grading the amount of support needed to rise.

### Potential Determinants

We will explore the following potential determinants for the components of sarcopenia and physical frailty: sex, age, weight Z-scores at diagnosis, time since the start of treatment, registered toxicity and serious adverse events in induction therapy, cumulative vincristine dosage, dexamethasone pharmacokinetics, and carrier of relevant genetic variants (candidate single-nucleotide polymorphisms). Information regarding these factors will be extracted from the electronic patient files or is collected in the DexaDays-2 study. Dexamethasone kinetics are measured through peak levels (2-3 hours after the first dexamethasone administration on day 1 of the dexamethasone course) and trough levels (measured on day 6, at least 12 hours after the last dexamethasone dose administered on the previous evening). A peripheral blood sample to extract germline DNA, for evaluation of carrier status of relevant candidate single-nucleotide polymorphisms related to sarcopenia and physical frailty, is taken on T1 as part of the DexaDays-2 study. As a complete array (Illumina GSA) will be run, we will be able to select the most relevant specific additional single-nucleotide polymorphisms of interest, based on evidence from the most recent literature (Figure 1).

### Statistical Analysis

The results of the physical frailty assessments, that is, SMI, handgrip strength, self-reported fatigue, walking speed, and physical activity (component scores), will be reported as means and SDs, or as median and interquartile ranges if data are non-normally distributed. The frequency of sarcopenia and physical frailty, as well as the individual components at all timepoints will be reported in percentages and schematically visualized. A correlation matrix will be built to explore coherence between the additional measure TRF and the other frailty components.

To evaluate the potential change in frailty components after 5 days of dexamethasone administration, a paired Student *t* test or Mann-Whitney *U* test will be used depending on the distribution of the data.

To evaluate whether the mean scores from the frailty components change between T1, T3, T7, and T11, 1-way ANOVA will be employed.

To study the effect of dexamethasone administration at T1, T3, T7, and prior to T11 on sarcopenia, physical frailty, and each individual components, generalized mixed models will be estimated. These models incorporate correlations between repeated responses on the same individual. Patient-specific random intercept, age, weight, time since the start of therapy, and cumulative vincristine dosage will be included in the model.

Multivariable linear regression model will be estimated to investigate associations between the potential determinants (patient- and treatment-related factors, pharmacokinetics, and genetics) and the assessment scores at T1 and T2 (SMI, handgrip strength, self-reported fatigue, walking speed, TRF, and physical activity). Results will be presented as regression coefficients along with 95% CI.

Multivariable logistic regression models will be estimated to explore associations between the aforementioned potential determinants and the occurrence of sarcopenia and physical frailty at T1 and T2. Odds ratios along with 95% CIs will be estimated.

Statistical analyses will be performed using software packages R Statistics (version 1.0.143; R Foundation) and SPSS (version 26.0.0.1) for Windows (IBM).

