**Methods:**

This prospective study is being pursued within the framework of the DexaDays-2 study: a randomized controlled trial on neurobehavioral side effects in pediatric patients with ALL. A total of 105 children (3-18 years) undergoing ALL maintenance treatment at the Princess Máxima Center for Pediatric Oncology are included in this study. Sarcopenia/frailty assessments are performed before and just after a 5-day dexamethasone course. A subset of 50 children participating in the DexaDays-2 trial because of severe dexamethasone-induced neurobehavioral problems were assessed at 3 additional timepoints. The sarcopenia/frailty assessment consists of bioimpedance analysis (skeletal muscle mass [SMM]), handheld dynamometry (handgrip strength), Pediatric Quality of Life Inventory Multidimensional Fatigue Scale (fatigue), Timed Up and Go Test (TUG; walking speed), and physical activity questionnaires. To evaluate potential change in sarcopenia/frailty components after a 5-day dexamethasone administration, a paired Student t test or Mann-Whitney U test will be used. Because of the presence of repeated measurements, generalized linear mixed models will be used to estimate the effect of dexamethasone on sarcopenia and frailty outcomes. Multivariable regression models will be estimated to investigate associations between the assessment scores and patient and treatment-related factors.

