A total of 105 patients will undergo a physical frailty assessment before (T1) and after 5 days (T2) of dexamethasone administration (6 mg/m^2^ per day in 3 dosages). A subset of 50 children will be assessed at 3 additional timepoints (T3, T7, and T11), to observe the process of sarcopenia and physical frailty longitudinally. This subset comprised children participating in the DexaDays-2 randomized controlled trial based on the severity of their neurobehavioral problems. These 50 patients will receive physiological dosages of hydrocortisone or placebo during a 5-day dexamethasone treatment, and the cross-over will take place after 2 courses of dexamethasone treatment. The sample size is based on the DexaDays-2 study power calculation [40].

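### The non-normal fallback for the paired T1-T2 comparison is the Mann-Whitney U test, which is for independent groups and can lose most of its power when within-child correlation is high and the shift is small

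*Protocol article*

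**What the plan says.** The design gives two measurements per child (Study Design and Patient Recruitment): "A total of 105 patients will undergo a physical frailty assessment before (T1) and after 5 days (T2) of dexamethasone administration".

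For the change between these two assessments, the Statistical Analysis section plans that "a paired Student *t* test or Mann-Whitney *U* test will be used depending on the distribution of the data". The Methods part of the abstract has the same pair of tests: "a paired Student t test or Mann-Whitney U test will be used". No section names the Wilcoxon signed-rank test or any other paired rank test.

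The dexamethasone effect is also to be studied with generalized mixed models that have a patient random intercept. The Statistical Analysis section lists T1, T3, T7 and the period before T11 for these models and does not mention T2.

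The article takes its sample size from the parent trial's power calculation. It gives no effect size, SD, alpha or power for the T1-T2 comparison.

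**The concern.** The paired t test and the Mann-Whitney U test are not alternatives for the same data structure. The first works on within-child differences. The second compares two independent samples and treats the 105 T1 values and the 105 T2 values as if they came from 210 different children. Variation between children, which cancels in the differences, then goes back into the error term. Across ages 3 to 18 that variation may be large.

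Evaluating the effect of dexamethasone is one of the study's three aims, and T1-T2 is the before-and-after comparison planned in all 105 children. If a component is judged non-normal, its p-value comes from a test whose nominal 5% level is far above its true level when the correlation is positive. A small but real change over the course could then be reported as no change.

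**Working it through.** **Inputs from the article.** There are 105 pairs. The test-retest ICCs are 0.91-0.93 for handgrip (Muscle Strength), 0.80-0.98 for TUG (Walking Speed) and 0.68-0.84 for the PedsQL fatigue scale (Fatigue). For muscle mass there is only the statement "The Tanita device has shown excellent test-retest reliability", without a figure. Physical activity has no reliability figure.

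**Assumptions, because the article does not give them.** Two-sided alpha is 0.05. The T1-T2 correlation is ρ, varied. The shift δ is in between-child SD units, varied. The article states no power for this comparison, so there is no figure to reproduce.

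**Step 1: normal approximation.** With equal variances at T1 and T2:

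- True SE of the mean change: √(2(1−ρ)/105).
- SE implied by treating the samples as independent: √(2/105) = 0.138, so the observed shift must exceed 1.96 × 0.138 = 0.2705 SD.
- Power of the independent-groups test ≈ Φ[(δ − 0.2705)/true SE].
- Power of the paired test ≈ Φ[δ/true SE − 1.96].
- True type I error of the independent-groups test = 2[1 − Φ(1.96/√(1−ρ))].

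For ρ = 0.8 and δ = 0.2, the true SE is √(0.4/105) = 0.0617. The independent-groups power is Φ[(0.2 − 0.2705)/0.0617] = Φ(−1.14) = 13%. The paired power is Φ[0.2/0.0617 − 1.96] = Φ(1.28) = 90%.

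The type I error is 1.9% at ρ = 0.3, 0.6% at 0.5, 0.05% at 0.68 and about 0.001% at 0.80.

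**Step 2: simulation of the rank tests, 105 pairs, δ = 0.2 SD.**

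| ρ | Mann-Whitney U | Signed-rank |
|---|---|---|
| 0.7 | 17% | 73% |
| 0.8 | 13% | 88% |
| 0.9 | 8% | 99% |

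At these correlations the type I error of the Mann-Whitney test is about 0.

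**Step 3: skewed data.** Lognormal pairs (log-SD 0.5, shift of 0.2 SD on the log scale, 4000 runs per setting) give the same picture. Mann-Whitney against signed-rank is 17% v 67% at ρ = 0.68, 12% v 85% at 0.80 and 6% v 99.6% at 0.91.

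**Step 4: where the loss shrinks.**

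- Larger shifts: at 0.3 SD and ρ of 0.7 to 0.9, Mann-Whitney has 61-70% against 97-100%. At 0.5 SD both tests have 99.5% or more at ρ of 0.68 and above (lognormal runs).
- Lower correlation, 0.2 SD, lognormal runs: 22% v 48% at ρ = 0.5, 26% v 37% at 0.3 and 29% v 27% at 0.

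**The case against.** The strongest reply is that the harm is conditional several times over, and most of that stands.

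- **Only a fallback.** Components judged normal get the paired t test, which is valid. The article gives no distributional information, so how many components would go to the fallback is unknown.
- **Conservative direction.** With positive correlation the error does not create false positives. The frequencies of sarcopenia and frailty, and the regressions on determinants, do not depend on it.
- **Proxy correlations.** A test-retest ICC is not the correlation across a dexamethasone course. If children respond differently, the T1-T2 correlation will be lower and the loss smaller.
- **Other analyses.** The planned mixed models respect within-child correlation. They cannot be counted on to repair this comparison, because the text does not say that T2 enters them. Even if it does, the separate T1-T2 p-value would still come from the wrong test.

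A reader might infer that most of the power is lost on every skewed component. The article does not support that: the result depends on a correlation and a shift that it does not state, and SMI and physical activity have no reliability figure at all. A reader might also take T1-T2 as the main dexamethasone comparison, but no comparison is designated primary. Nor does the point reach the rising-from-the-floor times: the planned sentence covers frailty components, and that test is described as an additional measure.

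None of this makes the named test right for paired data.

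**Conclusion.** Wrong as written. The article names an independent-groups test, in two places, for measurements on the same children, and nothing elsewhere corrects it. An unseen analysis plan does not explain this away, because the article positively names the test.

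The consequence is a possible loss of power for components sent to the fallback, not a certain one. It is severe for a shift near 0.2 SD with a correlation of 0.7 or more, moderate at 0.3 SD and negligible at 0.5 SD. It is also smaller at lower correlations. These sizes rest on the assumed shift and correlation and on a two-sided 5% level. The ICC range of 0.68 to 0.98 for grip, TUG and fatigue makes a high correlation plausible for those three but does not establish it.

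**What to change.** In the Methods part of the abstract and in the Statistical Analysis section, replace the Mann-Whitney U test by the Wilcoxon signed-rank test. State that the choice between the paired t test and the signed-rank test depends on the distribution of the within-child T2-T1 differences. The present wording refers only to the distribution of the data, and raw scores over ages 3 to 18 may look non-normal when the differences do not.

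The cost is a change of test name in two places and one added clause. It needs no new data and no change to the assessments.

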## Methods

### Study Design and Patient Recruitment

This prospective national observational cohort study is taking place at the Princess Máxima Center for Pediatric Oncology, Utrecht, the Netherlands. The children included in this study are participating in the DexaDays-2 study: a randomized controlled trial on neurobehavioral side effects in pediatric patients with ALL [40]. In that study, Dutch patients with ALL are eligible when they fulfill the following criteria: age 3-18, confirmed diagnosis of ALL, and inclusion in the Dutch Childhood Oncology Group (DCOG) medium-risk group of the ALL-11 protocol. Only patients between 3 and 18 years can participate as this was an inclusion criterion for the DexaDays-2 study, because the questionnaires used in that study are validated only for those ages. Children who reach the age of 3 years during maintenance therapy and are still due to receive 5 dexamethasone courses after their birthday (at least 15 weeks before the end of therapy) are also eligible. Exclusion criteria of that study are anticipated compliance problems, underlying conditions that affect the absorption of oral medication, uncontrolled infections, or any other complications that may interfere with administering dexamethasone treatment, insufficient command of the Dutch language, preexisting mental retardation, and hydrocortisone or risperidone use during the invitation to participate.

Our study on sarcopenia and frailty is being pursued within the framework of the aforementioned DexaDays-2 study. The latter consists of 2 parts: an identification study (including 2 timepoints: T1-T2) and a randomized controlled trial (T3-T11). The prospective observations of the current study are performed at a subset of these time points (Figure 1) during 15 weeks of the maintenance phase of ALL therapy.

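### The choice of test for the T1-T2 change is not tied to the within-child differences, and its fallback ignores the pairing

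*Protocol article*

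**What the plan says.** The Statistical Analysis section introduces the T1-T2 comparison with the words "To evaluate the potential change in frailty components after 5 days of dexamethasone administration". It names two candidates, a paired Student t test and a Mann-Whitney U test, and gives the criterion: "test will be used depending on the distribution of the data". The Methods paragraph of the Abstract names the same pair without a criterion: "a paired Student t test or Mann-Whitney U test will be used".

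Neither place says which variable is examined. Earlier in the Statistical Analysis section the same word refers to the component scores, which are to be "reported as means and SDs, or as median and interquartile ranges if data are non-normally distributed".

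The comparison covers the whole cohort: "A total of 105 patients will undergo a physical frailty assessment before (T1) and after 5 days (T2) of dexamethasone administration". On age the recruitment section says: "Only patients between 3 and 18 years can participate".

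**The concern.** A paired t test makes no assumption about the shape of the scores at T1 or at T2. It depends only on the differences T2 minus T1. A rule that looks at the raw scores can therefore reject the paired t test for a reason that has nothing to do with its validity. In a cohort from preschool age to 18 years, a score that rises with growth is spread and often skewed by age alone, whatever dexamethasone does.

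The destination of the switch makes this worse. Mann-Whitney U compares two independent groups. Applied to T1 and T2 in the same children, it sets the 5-day change against the full between-child spread and discards the pairing. At stake is the before/after comparison around one dexamethasone course in all 105 children, which serves the second aim.

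**Working it through.** The article gives no figure on this point, so there is nothing to reproduce. The check has four steps.

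**Inputs from the article.** 105 pairs; ages 3 to 18; handgrip in kilograms (Muscle Strength); Timed Up and Go as a time (Walking Speed); muscle mass already indexed to height (Skeletal Muscle Mass).

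**Assumed inputs.** Two-sided 5% level; true shift of 0.3 SD of the difference; Shapiro-Wilk at 5% as the normality check, with a switch if T1 or T2 fails; ages uniform or skewed to the young. The handgrip-like score has a mean of 2 + 2 × (age − 3) kg and a between-child SD of 20% of the mean. The SD of the difference is either constant (20% of the total SD) or proportional to the child's score (10%), with the shift scaled likewise. The resulting T1-T2 correlation is about 0.98.

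**Step 1: the relevant distribution.** The paired statistic is t = mean(d) / (SD(d)/√n) with d = T2 − T1. The T1 and T2 distributions enter only through d.

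**Step 2: what the wording points to.** Two cues favour raw scores: the earlier use of the word for component scores, and a fallback that takes two sets of scores and has no natural form on one set of differences. One cue favours differences: the sentence is about change. The text does not settle it.

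**Step 3: simulation** (2,000 runs per row, shift 0.3). The last column applies the raw-score rule with Mann-Whitney U as fallback.

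| Score, ages | Raw scores fail normality | Differences fail | Power, paired t | Power, signed-rank | Power, rule |
|---|---|---|---|---|---|
| Handgrip, constant, uniform | 0.907 | 0.058 | 0.864 | 0.850 | 0.078 |
| Handgrip, constant, young | 0.999 | 0.051 | 0.860 | 0.842 | 0.000 |
| Handgrip, proportional, uniform | 0.958 | 0.894 | 0.746 | 0.778 | 0.032 |
| Handgrip, proportional, young | 1.000 | 0.950 | 0.736 | 0.793 | 0.000 |
| Height-indexed muscle, uniform | 0.054 | 0.046 | 0.852 | 0.845 | 0.808 |
| Height-indexed muscle, young | 0.084 | 0.053 | 0.878 | 0.859 | 0.810 |
| Age-standardised, uniform | 0.062 | 0.046 | 0.851 | 0.832 | 0.798 |
| Age-standardised, young | 0.072 | 0.050 | 0.856 | 0.841 | 0.793 |

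With no true shift and proportional differences, the paired t test rejected in 0.044 and 0.052 of runs, so it held its level even though the differences were clearly non-normal.

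A second simulation (3,000 cohorts, other growth curves, within-child error constant up to fully proportional to size) included Timed Up and Go. Raw times failed normality in 64-98% of cohorts and raw handgrip in 99.7-100%. Power was 0.85-0.87 (Timed Up and Go) and 0.69-0.86 (handgrip) with the paired t test, and 0.00-0.07 after the switch to Mann-Whitney U. With a paired rank test as fallback, power changed by about −2 to +9 points.

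**Step 4: why the fallback costs so much.** By normal approximation, paired power is Φ(0.3 × √105 − 1.96) = Φ(3.074 − 1.96) = Φ(1.114) = 0.867. An unpaired test on data with correlation ρ has power of about Φ(3.074 − 1.96/√(1 − ρ)):

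- ρ = 0.5: Φ(3.074 − 2.772) = 0.62
- ρ = 0.7: Φ(3.074 − 3.578) = 0.31
- ρ = 0.8: Φ(3.074 − 4.383) = 0.10
- ρ = 0.9: Φ(3.074 − 6.198) = 0.001

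Its true type I error, 2 × (1 − Φ(1.96/√(1 − ρ))), is 0.006 or less throughout.

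**The case against.** The strongest reply is that the article never says raw scores are checked. The sentence concerns change, a paired t test works on differences, and the variable used for a normality check is a detail that a condensed article may leave to the full plan. This stands in part: a reader might infer that the plan examines scores rather than differences, and the text does not establish that. But the article does state a switching criterion and its fallback. The criterion as worded lets the wrong variable decide, and the fallback is the wrong type of test on either reading.

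Four further points stand and limit the finding:

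- A reader might infer that most components would lose the paired t test. The documents do not support this. Muscle mass is height-indexed, fatigue is a questionnaire score, and handgrip and Timed Up and Go are compared with age-related references, although the analysis section does not say that standardised values enter the test.
- The large power loss belongs to the unpaired fallback, not to the choice of variable to check.
- Moving the check to the differences would not always keep the t test. If change scales with size, the differences fail normality too.
- In that case a mean change in kilograms also depends on the age mix, so this dependence is no argument against the switching rule alone.

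Aim 2 does not rest on this test alone either, since mixed models are also planned. Their sentence names T1, T3, T7 and T11 but not T2, and the timeline figure is not shown, so how far they cover the 5-day change cannot be judged.

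**Conclusion.** The point holds in a limited form. The rule does not tie the distribution check to the within-child differences, and it leads to a test that ignores the pairing. If raw scores are checked, handgrip in kilograms over ages 3 to 18 would leave the paired t test in about 90% or more of simulated cohorts. Power would then fall from about 0.86 to below 0.1 with constant-size differences, or from about 0.74 to 0.03 or less with proportional ones.

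These figures rest on the assumed shift, growth curve, age distribution and normality test. A fall to about 0.1 or lower needs a T1-T2 correlation of roughly 0.8 or more; at 0.5 the unpaired test would still have power of about 0.62. With a signed-rank fallback the difference from the paired t test is small, from about 2 points lower to 9 points higher.

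For Timed Up and Go the switch depends on the assumptions. An age-driven switch is not shown for the muscle index, fatigue or age-standardised scores. In the simulated muscle-index and age-standardised rows the rule costs only 4 to 7 points.

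**What to change.** In the Statistical Analysis section, and to match in the Abstract, state three things:

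1. The T1-T2 change in each component is analysed on the within-child difference, with a paired t test and a 95% CI as the main analysis.
2. Any check of distribution is made on these differences.
3. The Wilcoxon signed-rank test replaces Mann-Whitney U and serves as a sensitivity check.

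Naming the main analysis in advance matters more than moving the check, because non-normal differences could still trigger a switch although the t test holds its level in the simulated cases with 105 pairs. The cost is a sentence or two of wording; no new data are needed.

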Some possible study limitations have to be taken into account as well. We will only include children participating in the DexaDays-2 study, which could potentially lead to selection bias, as patients who experience dexamethasone-induced neurobehavioral problems could be more motivated to participate because in that trial they will receive a drug to potentially reduce these problems. Furthermore, the subset of 50 children that will be measured longitudinally comprises children participating in the DexaDays-2 randomized controlled trial based on the severity of their neurobehavioral problems. These patients will receive physiological dosages of hydrocortisone or placebo during a 5-day dexamethasone treatment, and the cross-over will take place after 2 courses of dexamethasone treatment. We do not know if this affects the occurrence of sarcopenia and physical frailty in this cohort, for example, whether children with dexamethasone-induced clinically relevant neurobehavioral problems also show more physical side effects. Besides, within the DexaDays-2 study patients aged 3-18 years were selected, which complicated selecting outcome measures suitable for all participants. We succeeded in selecting measurements that have previously been used and validated in pediatric populations indicating their usefulness; however, with the exception of the PedsQL-MFS, none of the measurements has been validated in pediatric oncology patients.

In conclusion, this study is designed to determine the occurrence and severity of sarcopenia and frailty components in children during the maintenance phase of ALL therapy, and to determine the effects of administration of high doses of dexamethasone on physical vulnerability. With this study we aim to create awareness about these potential risks in children with ALL, as well as expanding our knowledge for reducing further side effects.

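### One-way ANOVA is the wrong test for change across T1, T3, T7 and T11: the visits are repeated measurements on the same children, and T1 also includes 55 children with no later visit

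*Protocol article*

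**What the plan says.** Under Statistical Analysis, change in the component means across visits is assigned to a named test: "To evaluate whether the mean scores from the frailty components change between T1, T3, T7, and T11, 1-way ANOVA will be employed". Neither a repeated-measures version nor a within-child term is mentioned, and the children who supply the T1 values are not specified.

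Study Design and Patient Recruitment fixes who is measured when. For the first two visits: "A total of 105 patients will undergo a physical frailty assessment before (T1) and after 5 days (T2) of dexamethasone administration". For the later ones: "A subset of 50 children will be assessed at 3 additional timepoints (T3, T7, and T11"). The later group is not a random sample: "This subset comprised children participating in the DexaDays-2 randomized controlled trial based on the severity of their neurobehavioral problems".

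The paragraph after the ANOVA plans generalized mixed models with a patient random intercept for the effect of dexamethasone administration, and says of them: "These models incorporate correlations between repeated responses on the same individual". On descriptive reporting, the same section says: "The frequency of sarcopenia and physical frailty, as well as the individual components at all timepoints will be reported in percentages".

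**The concern.** There are two separate faults.

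**Error term.** One-way ANOVA assumes that the groups compared are independent. Here each of the 50 children contributes to all four visits. Stable differences between children (age, size, baseline strength) stay in the error term, although they cancel when a child is compared with himself or herself. The plan recognises the correlation one paragraph later but does not use it here.

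**Population.** T1 exists for 105 children and the later visits for a selected 50. Nothing limits the T1 group to those 50. If all 105 enter, a standing difference between selected and unselected children shows up as change over time. The Discussion says it is unknown "whether children with dexamethasone-induced clinically relevant neurobehavioral problems also show more physical side effects", so the authors cannot assume that this difference is zero. Percentages over time would have the same problem if T1 and T2 for 105 children are set beside T3 to T11 for 50.

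At stake is the longitudinal reading of the study. A non-significant ANOVA could be taken as evidence that muscle and function are stable over repeated dexamethasone courses when the test had almost no power to show otherwise. A significant one could reflect only who was followed.

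**Working it through.** The article states no alpha, power, effect size, SD or within-child correlation for this test and takes its sample size from the parent trial, so there is no figure to reproduce.

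**Inputs from the article:** 105 children at T1; 50 of them at T3, T7 and T11; hence 105 − 50 = 55 with no later visit.

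**Assumptions:** total SD 1; equal correlation ρ between visits of 0.5, 0.7 or 0.9; alpha 0.05; no dropout. The article's test-retest coefficients (handgrip 0.91-0.93, fatigue 0.68-0.84, Timed Up and Go 0.80-0.98) make high correlation plausible. Correlation over 15 weeks may be lower, so the range starts at 0.5.

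**Step 1: what goes wrong with F in the same 50 children.** With no change, the expected mean square between visits is (1 − ρ)σ². One-way ANOVA divides it by a within-visit mean square whose expectation is σ². A repeated-measures analysis divides it by a residual whose expectation is (1 − ρ)σ². So the one-way F centres near 1 − ρ instead of 1. The one-way 5% critical value on 3 and 4 × 50 − 4 = 196 degrees of freedom is 2.65. To reach it, the repeated-measures F would have to be about 2.65/(1 − ρ):

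- ρ = 0.5: 5.3
- ρ = 0.7: 8.8
- ρ = 0.9: 26.5

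At ρ = 0.5, the chance of F(3,147) exceeding 5.3 is about 0.17%.

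**Step 2: power for a linear change of 0.3 SD from T1 to T11.** The visit means are 0, 0.1, 0.2 and 0.3, with squared deviations summing to 0.0225 + 0.0025 + 0.0025 + 0.0225 = 0.05. The repeated-measures noncentrality is 50 × 0.05/(1 − ρ) = 5.0, 8.3 and 25. The noncentral F on 3 and 147 degrees of freedom then gives power of 43%, 66% and 99%.

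**Step 3: Monte Carlo, 5,000 replicates per scenario, same 50 children.**

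| ρ | One-way, no change | Repeated measures, no change | One-way, 0.3 SD change | Repeated measures, 0.3 SD change |
|---|---|---|---|---|
| 0.5 | 0.2% | 5.3% | 9% | 45% |
| 0.7 | 0.04% | 5.1% | 4% | 66% |
| 0.9 | 0.0% | 4.8% | 0.2% | 99% |

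The simulation agrees closely with steps 1 and 2.

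**Step 4: all 105 at T1, 50 later, no true change.** Let the 50 differ from the other 55 by δ SD at every visit. Relative to the 55, the T1 mean is δ × 50/105 and each later mean is δ. The apparent change is therefore δ × 55/105.

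| δ | Apparent change | One-way rejection rate, ρ from 0.5 to 0.9 |
|---|---|---|
| 0 | 0 | 0.7% to 0.1% |
| 0.3 | 0.16 SD | 7% to 3% |
| 0.5 | 0.26 SD | 27% to 19% |
| 0.8 | 0.42 SD | 73% to 68% |

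In the same scenarios, repeated-measures ANOVA restricted to the 50 rejects 4.3% to 5.4% of the time.

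**The case against.** The strongest reply is that the mixed models already cover this. They use the same outcomes, nearly the same visits and a patient random intercept, and the abstract names mixed models for the repeated measurements without mentioning ANOVA. On that view the ANOVA is a supporting test. This softens the consequence for the dexamethasone aim. But the models are assigned to the effect of dexamethasone administration, not to change in means between visits, and are not said to replace the ANOVA.

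A second reply is that the authors mean repeated-measures ANOVA in the 50, since that subset is followed for the longitudinal question, and that the analysis set may be defined in a fuller document. That is possible. However, the preceding paragraph calls its t test paired, so pairing is stated where intended, and a repeated-measures reading would still leave open which children supply T1.

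The remaining points limit the size of the finding, and they stand. Within the 50 the error is conservative: it hides change and does not invent it. The selection problem needs both all 105 at T1 and a real difference between the groups. At 0.3 SD the rejection rate is about nominal, and the documents give no evidence that the difference is larger. The power loss depends strongly on a correlation that the article does not report. Showing percentages separately for the 50 prevents a misreading in tables; the sentence on percentages is not itself an error.

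**Conclusion.** The concern holds and should be corrected before the longitudinal analysis is run. The error-term fault is firm: it arises with any positive within-child correlation and does not depend on selection. For correlations from 0.5 to 0.9, the type I error is about 0.2% or less instead of 5%, and power for a 0.3 SD change falls from 45-99% to 9-0.2%. The selection fault is conditional: the article does not exclude it, and its size is 55/105 of whatever difference exists between the 50 and the other 55. All correlations, changes and group differences used here are assumptions, shown as ranges, with equal correlation between visits and no dropout.

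**What to change.** Replace the one-way ANOVA by a linear mixed model for each component score, with visit (T1, T3, T7, T11) as a categorical fixed effect and a child random intercept, fitted in the 50 longitudinal children. Repeated-measures ANOVA in the same 50 would also serve. State explicitly that T1 in this analysis comes from those 50 only. Report the contrasts of T3, T7 and T11 with T1, with 95% confidence intervals. In tables and figures of percentages over time, show T1 and T2 for the 50 separately from T1 and T2 for all 105.

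The cost is a change of analysis wording. No new data are needed, and mixed models with a patient random intercept are already planned.
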